### Confidentiality, data management and access

All data will be stored using numbers to identify participants at the secured databases of Leiden University and Wageningen University and Research. Only one document exists that links participant numbers to personal data, and this file is only available to the main researchers performing data collection at Leiden University and Wageningen University. Data that need to be entered manually (e.g., measured weight and height during home visits, codes of video material) will be entered in the latest version of the statistical software package IBM SPSS Statistics by trained researchers/students. The quality of this data entry will be checked regularly by another (independent) trained researcher/student.

As detailed in the consortium agreement-contract of the project, only researchers and students involved in the project working at any of the academic parties (Leiden University, Wageningen University and Research) will be allowed access to the data. With the exception of the video-recordings (VIPP-FI), which contain privacy-sensitive information, research data will be open access where possible (e.g. when a peer-reviewed journal requests or offers the uploading of anonymized datasets into an open access database. In these cases, all personal information will be removed from data files and replaced by participant identification numbers. The file linking these numbers to personal information will be stored digitally in a separate password protected file that will only be accessible to the researchers). Large video-files will be shared between the two universities by making copies on external pass-word protected hard-drives and personally exchanging these hard-drives.

### Analyses

The intention-to-treat principle will be applied to all analyses. Whether the interventions differentially affect primary and secondary outcomes over time will be analyzed using linear mixed models analyses, a technique that makes use of every data point for every participant, irrespective of their missing data. The three intervention groups will be compared to the control group, and the combined group will be compared to the repeated exposure and the VIPP-FI group. A significance level of α = .05 will be used. The analyses will be corrected for relevant covariates such as family socioeconomic status, maternal consumption of vegetables, parental body mass index (BMI), child temperament, etc.

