## Abstract

**Background:**

The start of complementary feeding in infancy plays an essential role in promoting healthy eating habits. Evidence shows that it is important *what* infants are offered during this first introduction of solid foods: e.g. starting exclusively with vegetables is more successful for vegetable acceptance than starting with fruits. *How* infants are introduced to solid foods also matters: if parents are sensitive and responsive to infant cues during feeding, this may promote self-regulation of energy intake and a healthy weight. However, the effectiveness of the *what* and the *how* of complementary feeding has never been experimentally tested in the same study. In the current project the *what* and *how* (and their combination) are tested in one study to determine their relative importance for fostering vegetable acceptance and self-regulation of energy intake in infants.

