### Aims and hypotheses

In summary, the *Baby’s First Bites (BFB)* study aims to test whether promoting the *what* and**/**or promoting the *how* of complementary feeding will result in increased vegetable consumption and liking and a better self-regulation of energy intake in infants and toddlers up until the age of 36 months. To this end, we will perform a superiority randomized controlled trial with parallel groups, comparing a) an intervention focusing on vegetable exposure (=what), b) an intervention focusing on sensitive feeding (=how), c) an intervention focusing on vegetable exposure and sensitive feeding (=what and how), and d) a control condition. The interventions will begin when the infant starts receiving complementary food (child age 4–6 months, as recommended by the Dutch Nutrition Center) and continue until the child is 16 months old. We hypothesize that a) all interventions are more effective in improving vegetable consumption and vegetable liking than the control condition without guidance on complementary feeding; b) the sensitive feeding and combined intervention will be more effective in supporting child self-regulation of energy intake than the vegetable exposure or control conditions; and c) the combined intervention is more effective than the other two interventions alone in promoting vegetable intake and vegetable liking. As the inclusion phase of the *BFB* study has already successfully been completed, the present article describes the characteristics of the sample of included participants as well as the design of this ongoing study.

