### Calculation of sample size

A power analysis was conducted to calculate the sample size necessary to detect a moderate effect size of .50, which is based on previous studies of the effects of repeated exposure to vegetables [27] and the effects of VIPP [72]. Given a power of .80 and an alpha of .05 the analysis showed that a sample size of 51 participants per group would be sufficient. Taking attrition into account, we aimed to include a total of 240 mothers, 60 per group (see Fig. 1 and Table 1).

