## Discussion

*Baby’s First Bites* will be the first trial explicitly testing the separate and combined effects of promoting the *what* and *how* of complementary feeding. By comparing three prolonged, intensive interventions, we will be able to draw firm conclusions on what is most important to focus on when promoting vegetable acceptance and children’s self-regulation of energy intake in early childhood; what food to offer, how to offer this food, or a combination of the two. Moreover, this will be the first trial to include an intervention specifically manipulating sensitive feeding practices without manipulating any other variables, evaluating its effects using both self-report and observational measures. This allows conclusions on whether this parenting practice will indeed promote healthier food preferences in children and will foster children’s ability to self-regulate their energy intake, as is often suggested in the literature.

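### The planned contrasts omit VIPP-FI versus RVE, so hypothesis (b) is only partly tested and the direct what-versus-how comparison has no planned test

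*Protocol article*

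**What the plan says.** The Analyses section of the protocol article commits to linear mixed models and then names the comparisons: "three intervention groups will be compared to the control group, and the combined group will be compared to the repeated exposure and the VIPP-FI group". No other between-arm comparison is named there.

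The Aims and hypotheses section states as hypothesis (b) that "the sensitive feeding and combined intervention will be more effective in supporting child self-regulation of energy intake than the vegetable exposure or control conditions". The abstract's Methods paragraph lists self-regulation of energy intake among the primary outcomes.

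Two further places set out what the trial is for. The abstract's Background says the components and their combination are studied in one trial "to determine their relative importance for fostering vegetable acceptance and self-regulation of energy intake in infants". The Discussion says that by comparing the three interventions "we will be able to draw firm conclusions on what is most important to focus on", and goes on to name the choice: what food to offer, how to offer it, or both.

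The sample size section plans "to detect a moderate effect size of .50" with power .80 and alpha .05, giving 51 per group, raised to 60 for attrition. It does not say whether the test is one-sided or two-sided.

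**The concern.** The article's list of comparisons does not match its own hypotheses. Hypothesis (b) names the vegetable-exposure arm as a comparator for the sensitive feeding arm, and that pair is the one left off the list. It is also the only pair that sets *what* alone against *how* alone.

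Two things are at stake. One component of a pre-stated hypothesis on a primary outcome has no pre-stated test; if it is added once data have been seen, it will be post hoc. And the ranking of *what* against *how* has no planned test of its own. A statement that one matters more than the other could then only be drawn indirectly, for example because one arm differs significantly from control and the other does not. That is not a test of the difference between them.

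**Working it through.** **Step 1. Count the pairs.** Four arms give 4 × 3 / 2 = 6 pairs. Setting the Analyses section beside hypothesis (b), read arm by arm:

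| Pair | Planned in Analyses | Needed for (b) |
|---|---|---|
| RVE vs AC | yes | no |
| VIPP-FI vs AC | yes | yes |
| COMBI vs AC | yes | yes |
| COMBI vs RVE | yes | yes |
| COMBI vs VIPP-FI | yes | no |
| VIPP-FI vs RVE | **no** | **yes** |

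Five of six pairs are planned, and three of the four that (b) needs.

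**Step 2. Reproduce the stated sample size.** Inputs from the sample size section: d = 0.50 (taken as a difference in means with SD = 1), power 0.80, alpha 0.05. Formula: n per group = 2(z_alpha + z_power)² / d².

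- One-sided: 2 × (1.645 + 0.842)² / 0.25 ≈ 49.5, so 50. The exact t-test gives 50.15, so 51.
- Two-sided: 2 × (1.960 + 0.842)² / 0.25 ≈ 62.8, so 63. The exact t-test gives 63.77, so 64.

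The stated 51 is the one-sided, single-pair figure with no multiplicity adjustment. Since sidedness is not stated, both versions are carried below.

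**Step 3. Power of the omitted pair at 51 versus 51.** The standard error is √(2/51) = 0.198, so d/SE = 0.50/0.198 = 2.525.

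- Two-sided: Φ(2.525 − 1.960) = Φ(0.565) ≈ 0.71 (exact t: 0.706).
- One-sided: Φ(2.525 − 1.645) = Φ(0.880) ≈ 0.81 (exact t: 0.806).
- With no attrition (60 versus 60): about 0.78 two-sided and 0.86 one-sided.

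The same figures apply to each pair already on the list.

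**Step 4. What adding the pair does to (b) as a whole.** Suppose both *how* arms exceed both other arms by d = 0.50, with 51 per arm. By simulation, the three planned pairs are all significant in about 45% of trials (two-sided) or 60% (one-sided). For all four pairs the figures are 39% and 55%.

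**Step 5. Can pooling stand in for the missing pair?** Write R, V, C and A for the arm means of RVE, VIPP-FI, COMBI and AC.

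- Average *how* effect: (V + C)/2 − (R + A)/2. This compares 102 with 102, with power about 0.95 two-sided at d = 0.50.
- Average *what* effect: (R + C)/2 − (V + A)/2.
- Their difference: V − R. C and A cancel, so weighing *how* against *what* comes back to the omitted 51 versus 51 pair, and pooling brings no gain there.
- For (b): let R = V = A = 0 and C = 1.0. The average *how* effect is (0 + 1.0)/2 − 0 = 0.50, yet VIPP-FI does not differ from RVE or control. The pooled contrast would probably be significant while (b) is false for the VIPP-FI arm.

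These calculations compare means at one time point and ignore the repeated measures and covariates of the planned model.

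**The case against.** The best defence is that little is lost. The missing estimate follows from two planned ones, since (COMBI − RVE) − (COMBI − VIPP-FI) = VIPP-FI − RVE, and the same model yields its standard error. Hypotheses (a) and (c) make no prediction about this pair for vegetable intake or liking, and the aim and the promised conclusion stand in abstract and discussion prose. This stands as a limit on severity: the design and the data are untouched. It does not remove the mismatch, because (b) does name the pair and being able to compute an estimate is not the same as planning to test it.

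A separate analysis plan, not shown, might list more contrasts. But the article is not silent here: it states a list, and that list disagrees with its own hypothesis.

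A reader might infer that (b) goes untested. The documents do not support that: three of its four pairs are planned.

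A reader might also infer that (b) simply is the sensitive-feeding main effect of a 2 × 2 layout, and that the pairwise plan is wrong because it forgoes about 95% power. That does not follow either. Step 5 shows that the two claims differ, and the higher power belongs to the pooled contrast, not to the omitted pair. The article describes a trial with four parallel groups. COMBI receives five calls plus five visits, VIPP-FI visits only, and RVE and AC calls only (Table 1 and the COMBI section), so contact number and mode differ across the would-be factor. The section on repeated exposure and sensitive feeding expects the combination may be especially effective, which makes an interaction plausible. Pairwise contrasts are a defensible choice.

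**Conclusion.** The point holds as a mismatch between the stated contrasts and the stated hypotheses. One pair of six is missing. It is one of the four that hypothesis (b) needs on a primary outcome, and it is the only direct test of *what* against *how*. Hypothesis (b) is incompletely tested; the direct *what*-versus-*how* comparison has no planned test.

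The count rests on the article alone, with (b) read as each *how* arm against each of the other two arms. If (b) were instead read as one grouped comparison, the list would not contain that either. The power figures assume a standardized difference of 0.50, 51 evaluable families per arm and an unadjusted alpha of .05. The flaw is small to correct, but it bears on the question the trial says it will answer.

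**What to change.** In the Analyses section, add VIPP-FI versus RVE to the planned contrasts, estimated from the same mixed model. State its two uses: for hypothesis (b) on self-regulation, alongside VIPP-FI versus AC, COMBI versus AC and COMBI versus RVE; and for the *what*-versus-*how* conclusion. Any statement about which component matters more should rest on this estimate and its confidence interval.

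Optionally, report the pooled contrast (VIPP-FI + COMBI) versus (RVE + AC) on self-regulation as a supplementary estimate of the average *how* effect. Show it with the RVE-by-VIPP-FI interaction and a note on the unequal contact load and mode. It should not replace the pairwise tests of (b).

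The cost is one sentence and one more contrast, with no further families, visits or measurements. The added contrast has single-pair power only, and requiring all four pairs for (b) lowers the chance of full support somewhat (step 4). A non-significant result on this pair should therefore not be read as showing that *what* and *how* are equivalent.

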**Fig. 1 Fig1:**
[figure not shown]
General overview of study design

**Table 1 Tab1:** Overview of conditions and intended N per condition

Name	Description of condition	N
RVE	Repeated vegetable exposure intervention: - exposure to either green beans or cauliflower as target vegetable during the first 19 days of weaning - five phone calls to motivate parents to expose children to vegetables at child age 4–6, 8, 13 and 16 months	60
VIPP-FI	VIPP-Feeding Infants: - exposure to fruits and a sweet vegetable (carrots) during the first 19 days of weaning - five home-visits using video-feedback to promote sensitive feeding at child age 4–6, 8, 13 and 16 months	60
COMBI	Combination of RVE and VIPP-FI	60
AC	Attention control group: - exposure to fruits and a sweet vegetable (carrots) during the first 19 days of weaning - five phone calls on development of child at age 4–6, 8, 13 and 16 months	60

*Note*. *RE* Repeated exposure, *VIPP-FI* VIPP-Feeding infants, *COMBI* Repeated exposure and VIPP-Feeding infants combined, *AC* Attention-control condition

Intervention effects are assessed both during and after conclusion of the interventions by performing a pre-test at the first two days of complementary feeding (child age 4–6 months; *t*_*0*_), two assessments during the interventions (at the end of the 19-day feeding schedule (child age 5–7 months; *t*_*1*_) and when the child is 12 months old (*t*_*12*_)), a post-test at the age of 18 months (*t*_*18*_) and two follow-ups when the child is 24 (*t*_*24*_) and 36 months old (*t*_*36*_). *T*_*0*_ and *t*_*1*_ are not scheduled at a standard, fixed child age but rather within a certain age range because we wanted to allow parents to start complementary feeding when they thought their child was ready. The other measurements *are* scheduled at set child ages because the intervention sessions following the very first start of complementary feeding are scheduled at fixed time points (see *Timing of intervention sessions* below). The timeline for participants is depicted in Table 2. Participants are allowed to stop at any point during the study if they no longer want to participate. If participants decide to withdraw from the study, discontinue an intervention or are unable to complete a specific assessment, they will be asked once whether they would still be willing to complete (parts of) the intervention, the post-test and/or follow-up assessments to come.

**Table 2 Tab2:** Timeline for participants

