## Repeated exposure to a variation of vegetables (RVE)

The repeated vegetable exposure (RVE) intervention focuses on *what* to feed infants. The RVE intervention starts with vegetables only according to a 19-day feeding schedule as described by Barends and colleagues [26, 27], and further promotes vegetable exposure in the first year of complementary feeding until 16 months of age using a protocol developed specifically for the current study. We conducted a needs assessment and applied the Intervention Mapping (IM) process [78–80] to develop this protocol.

In short, to promote vegetable exposure in the first year of eating complementary foods the method of repeated exposure to vegetables is used because it has been found to be the most effective way to increase vegetable intake and liking in infants [40, 81]. To support this method, we motivate mothers both during and after the feeding schedule to offer their child vegetables daily. From an analysis of risk factors and determinants that may influence children’s vegetable consumption we selected the determinants *knowledge, attitude, self-efficacy, skills, modelling, availability of vegetables, beliefs of the parent, positive reinforcement,* and *costs* to target in the intervention.

The main goal of the RVE intervention is for mothers to increase the child’s acceptance and liking of vegetables by a) starting the first 19 days of complementary feeding with vegetables only and b) offer vegetables to their child daily after this first period. The risk factors and determinants described above are targeted with the feeding schedule and the five telephone calls. Each phone call focuses on a different theme (Table 4) and discusses basic information material and optional additional information material that is sent to mothers by post. Mothers are asked to read the basic information before the scheduled telephone call with the researcher. Conversations are structured according to the general principles of Motivational Interviewing (MI) [82]. Interveners are instructed to act as a coach and guide mothers through the feeding schedule and – during later sessions – the family meal. The telephone protocol contains guidelines with questions mothers might ask and possible responses.

**Table 4 Tab4:** Content of each of the RVE and VIPP-FI intervention sessions

Session	Child age	RVE			VIPP-FI	
		Theme	Topics discussed	Optional information	Situation filmed	Topics discussed

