1	4–6 m	Discovering vegetables	• Why should children learn to eat vegetables? • Keep offering, also if child rejects (at least 10 times)	• Benefits of eating vegetables • Development of taste in young children	Mother feeding infant pureed vegetables/fruits	Learn to observe and interpret child feeding cues (hunger, satiation, liking)
2	4–6 m	Keep on offering vegetables	• How long should I persist? (at least 10 times) • Daily variation, steady increase of portion size	• Tips about offering vegetables to children on a daily basis and the preparation of age appropriate vegetable meals	Mother feeding infant pureed vegetables/fruits	Five tips: Timing, routine, adequate pacing, stop at the right time, enjoy
3	8 m	Being creative with vegetables	• Increase level and variety of texture • Set a good example	• Additional information about introducing more lumpy foods to children. • Tips about preparing and storing age appropriate vegetable meals • Tips to cut costs	Child eating sandwich with mother; new topping on sandwich	What to do when infants a) want more autonomy during mealtimes and b) don’t want to eat
4	13 m	Vegetables are part of a balanced diet	• Eating with the whole family • Recommendations for vegetable intake	• Achieving the recommended intake for vegetables	Dinner with whole family; child is served a new vegetable	Positive ways of dealing with negative behavior during dinner
5	16 m	Keep eating vegetables	• Inform parents on possible food neophobia phase, and how to respond	• Involving children in the preparation of vegetables	Dinner with whole family; child is served something new	Inform parents on possible food neophobia phase, and how to respond to that

*Note.* m = months

The Stages of Change Model [83] is used to achieve behavior change. The model identifies five stages that people move through when modifying behavior; 1) pre-contemplation; 2) contemplation; 3) preparation; 4) action; 5) maintenance. During the first two sessions (during the 19 day feeding schedule) it is assumed that mothers are motivated to offer their child a vegetable puree daily (preparation/action phase). For session three to five, the stage of change is monitored based on the conversation with the mother. When the mother appears not to be motivated to offer vegetables or encounters barriers in doing so, the protocol contains a series of possible questions and arguments to be discussed to motivate or come up with solutions for the encountered barriers.

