#### Other measures

The following potential covariates will be assessed: demographic variables such as maternal and paternal education and job status, family income, cultural background (*t*_*0*_); type of milk feeding (breast/formula: *t*_*0*_*-t*_*18*_); maternal depression (*t*_*0*_*-t*_*36*_: Center for Epidemiologic Studies Depression Scale [101]); maternal vegetable intake (*t*_*12*_ and *t*_*36*_: Food frequency questionnaire [102]); maternal anthropometrics (*t*_*0*_*-t*_*36*_); use and amount of purée consumed of the 100 distributed vegetable- and fruit jars in the 5 months after the feeding schedule (*t*_*12*_); maternal self-efficacy related to feeding their child (*t*_*0*_*-t*_*36*_: Parental Feeding Self-Efficacy Questionnaire [103]); maternal emotions during feeding the child (*t*_*0*_*-t*_*36*_: measure designed for this study); structure of family meals (*t*_*0*_*-t*_*36*_: Meals in our Household [104]); maternal perception of feeding (*t*_*0*_*-t*_*36*_: Five Minute Speech Sample [105]); child temperament (*t*_*0*_*-t*_*12*_: Infant Behavior Questionnaire-Revised [106]; *t*_*18*_*-t*_*36*_: Early Childhood Behavior Questionnaire [107]); general parenting styles (*t*_*0*_*-t*_*36*_: observed maternal intrusiveness during mealtimes and observed maternal sensitivity and intrusiveness during free-play situations [95]; *t*_*18*_*-t*_*36*_: Comprehensive General Parenting Questionnaire [108]).

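### The effect models adjust for maternal vegetable consumption, which is measured only after randomisation and may lie on the path through which the vegetable-exposure intervention works

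*Protocol article*

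**What the plan says.** The Analyses section applies intention-to-treat throughout and uses linear mixed models for the primary and secondary outcomes, described as "a technique that makes use of every data point for every participant, irrespective of their missing data". It compares each intervention with control, and COMBI with RVE and with VIPP-FI. It then says the analyses will be "corrected for relevant covariates such as family socioeconomic status, maternal consumption of vegetables, parental body mass index (BMI), child temperament", and so on, without giving the time point of any covariate.

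The Other measures section gives the timing: "maternal vegetable intake (*t*_*12*_ and *t*_*36*_: Food frequency questionnaire". The other covariates named in Analyses have a value at t0: demographics are taken at t0, and maternal anthropometrics and child temperament are measured from t0 onwards.

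The Study design section describes the assessments at the end of the feeding schedule and at 12 months as "two assessments during the interventions". Table 2 places two sessions in the first 19 days and the others at 8, 13 and 16 months. The RVE section lists the determinants the intervention addresses, among them "skills, modelling, availability of vegetables, beliefs of the parent". In Table 4, one topic of RVE session 3 (8 months) is "Set a good example".

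**The concern.** A covariate in a randomised comparison should be fixed before the intervention can influence it. Maternal vegetable consumption is first recorded after three RVE sessions, and again after all five. If mothers in RVE and COMBI eat more vegetables because they were encouraged to model this, and their children eat more as a result, holding maternal intake constant subtracts that part of the benefit. The model then no longer estimates the total effect of assignment, which is what intention-to-treat is meant to deliver. Where something unmeasured drives both mother's and child's intake, adjustment can also distort the contrast with no direct mother-to-child path.

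The vegetable outcomes are primary, and the affected contrasts carry much of hypotheses (a) and (c) in Aims and hypotheses. There is also a practical consequence: a mixed model tolerates missing outcomes, but it does not by itself tolerate a missing covariate.

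**Working it through.** **1. The plan's own figure.** Calculation of sample size gives an effect of .50, power .80, alpha .05 and 51 per group. A one-sided two-sample t-test needs 50.15, rounded up to 51, with power .806 at 51. A two-sided test needs 63.77, so 64. The stated 51 is therefore the one-sided figure. That is a separate matter; it is used here only to express the loss on the plan's own scale. The step from 51 to 60 implies attrition of 1 - 51/60 = 15%.

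**2. Timing.** Sessions before t12: two in days 3–17 and one at 8 months, so three of five. Sessions before t36: all five. The weighed intake at t0 and t1 (child age 4–7 months) precedes the first maternal measurement by months.

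**3. Loss through the mediating path.** Let a be the shift in maternal intake caused by RVE (in SD) and b the slope of child intake on maternal intake within arm. With total effect .50, adjusted effect = .50 - a × b. The documents give neither a nor b; the values below are assumptions. Power is one-sided at 51 per group with the outcome SD held at 1, ignoring any precision gained from the covariate.

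| a | b | a × b | Adjusted effect | Share removed | Power |
|---|---|---|---|---|---|
| 0 | any | 0 | .50 | 0% | .81 |
| .1 | .1 | .01 | .49 | 2% | .79 |
| .2 | .2 | .04 | .46 | 8% | .75 |
| .3 | .3 | .09 | .41 | 18% | .66 |
| .5 | .4 | .20 | .30 | 40% | .44 |
| .5 | .5 | .25 | .25 | 50% | not computed |

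**4. Distortion without a direct path.** A simulation of 2,000,000 records gave mother and child a shared unmeasured cause (loadings .5 and .4) and no effect of maternal on child intake. The induced slope is .5 × .4 = .20, so the adjusted effect should be .50 - .20a. The simulation returned .46 for a = .2 and .40 for a = .5, against a true .50. With a = 0 there was no bias.

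**5. Which contrasts.** RVE vs AC, COMBI vs AC and COMBI vs VIPP-FI each set an arm with RVE against one without: three of the five planned comparisons. In COMBI vs RVE both arms receive RVE, so the shift should largely cancel. In VIPP-FI vs AC neither does, and the documents describe no comparable route.

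**6. Missing covariate.** If the t12 value enters the model and is not imputed, a family without it loses every row, including t0 and t1. The documents give no rate of loss before t12. Assumed losses of 5, 10, 15 and 20% of the 243 families that started are about 12, 24, 36 and 49 families. At 60 per arm, 57, 54, 51 and 48 remain, with one-sided power .84, .83, .81 and .78.

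**The case against.** The covariate list is illustrative, the article is condensed, and an analysis plan may exist that settles the details. RVE's stated goal is the child's acceptance and liking of vegetables; the mother's own intake is not named as a goal or determinant. Much of this stands, and it limits what can be claimed.

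- A reader might infer that the effects will be biased. The documents do not show this. The bias requires RVE to shift maternal intake, and they give no figure for that. The .25 case needs a shift of .5 SD in the mother's own diet, as large as the whole planned effect.
- A reader might infer that RVE directly targets maternal intake, or that all of the first three sessions teach modelling. The route is indirect, through modelling, availability and beliefs, and the advice to set an example appears in session 3 only.
- A reader might infer that early drop-outs are certain to be excluded and intention-to-treat breached. That follows only without imputation, which an analysis plan may specify. Families who withdraw are also asked once whether they will complete later assessments, so stopping early need not mean having no t12 value.
- A reader might extend the criticism to child temperament. A t0 value exists, and which time point enters the model is ordinary analysis-plan detail.

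None of this removes the core. Maternal vegetable consumption is explicitly named, and on the published schedule no baseline value exists for an analysis plan to choose. Imputing missing values would restore families but leave the covariate post-randomisation.

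**Conclusion.** The point holds in this form: the plan names a covariate for its intention-to-treat effect models that is measured only after randomisation, after at least three RVE sessions, and on a plausible pathway of RVE. For vegetable intake and liking, three of the five planned contrasts are exposed.

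Under the simple linear model in the working, the planned .50 becomes .46 with modest assumed inputs (a = b = .2), .41 with a = b = .3 and .25 at the extreme. It is unchanged by this path if RVE does not move maternal intake. These figures illustrate a range; they are not estimates from the trial. The loss of t0 and t1 rows is a second, conditional consequence: without imputation it would run against the claim that every data point is used. The documents give no grounds for extending the mediation argument to self-regulation of energy intake, where RVE alone is not hypothesised to work.

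**What to change.** Remove maternal vegetable consumption from the main effect models. Analyse it as a mediator or process outcome, or use it in a sensitivity analysis labelled as conditioning on a post-randomisation variable.

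Restrict adjustment in the main models to pre-intervention variables: the minimisation factors (age at start of complementary feeding, child gender, study location), socioeconomic status, and the t0 values of BMI and temperament. Table 2 places allocation before t0, so t0 values are pre-intervention rather than strictly pre-randomisation; the text should say so.

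The cost is one or two sentences in the Analyses section. No new data are needed, and the 12- and 36-month questionnaires keep their use.
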